## **8.6. Hospitalization**

Adverse events reported from studies associated with hospitalization or prolongation of hospitalization, are considered serious. Any initial admission (even if less than 24 hours) to a healthcare facility meets these criteria. Admission also includes transfer within the hospital to an acute/intensive care unit (eg, from the psychiatric wing to a medical floor, medical floor to a coronary care unit, neurological floor to a tuberculosis unit).

Hospitalization does not include the following:

- Rehabilitation facilities;
- Hospice facilities;
- Respite care (eg, caregiver relief);
- Skilled nursing facilities;
- Nursing homes;
- Routine emergency room admissions;
- Same day surgeries (as outpatient/same day/ambulatory procedures).

Hospitalization or prolongation of hospitalization in the absence of a precipitating, clinical adverse event is not in itself a serious adverse event. Examples include:

- Admission for treatment of a pre-existing condition not associated with the development of a new adverse event or with a worsening of the pre-existing condition (eg, for work-up of persistent pre-treatment lab abnormality);
- Social admission (eg, subject has no place to sleep);
- Administrative admission (eg, for yearly physical exam);

- Protocol-specified admission during a study (eg, for a procedure required by the study protocol);
- Optional admission not associated with a precipitating clinical adverse event (eg, for elective cosmetic surgery);
- Pre-planned treatments or surgical procedures should be noted in the baseline documentation for the entire protocol and/or for the individual subject.

Diagnostic and therapeutic non-invasive and invasive procedures, such as surgery, should not be reported as adverse events. However, the medical condition for which the procedure was performed should be reported if it meets the definition of an adverse event. For example, an acute appendicitis that begins during the adverse event reporting period should be reported as the adverse event, and the resulting appendectomy should be recorded as treatment of the adverse event.

### 8.7. Severity Assessment

**Table 3. Severity Assessment**

|                                                                                                                                                                                                                                                            |                                                          |
|------------------------------------------------------------------------------------------------------------------------------------------------------------------------------------------------------------------------------------------------------------|----------------------------------------------------------|
| If required on the adverse event case report forms, the investigator will use the adjectives MILD, MODERATE, or SEVERE to describe the maximum intensity of the adverse event. For purposes of consistency, these intensity grades are defined as follows: |                                                          |
| MILD                                                                                                                                                                                                                                                       | Does not interfere with subject's usual function.        |
| MODERATE                                                                                                                                                                                                                                                   | Interferes to some extent with subject's usual function. |
| SEVERE                                                                                                                                                                                                                                                     | Interferes significantly with subject's usual function.  |

Note the distinction between the severity and the seriousness of an adverse event. A severe event is not necessarily a serious event. For example, a headache may be severe (interferes significantly with subject's usual function) but would not be classified as serious unless it met one of the criteria for serious adverse events, listed above.

### 8.8. Causality Assessment

The investigator's assessment of causality must be provided for all adverse events (serious and non-serious); the investigator must record the causal relationship in the CRF, as appropriate, and report such an assessment in accordance with the serious adverse reporting requirements if applicable. An investigator's causality assessment is the determination of whether there exists a reasonable possibility that the investigational product caused or contributed to an adverse event. If the investigator does not know whether or not investigational product caused the event, then the event will be handled as "related to investigational product" for reporting purposes, as defined by the Sponsor (See Section on Reporting Requirements). If the investigator's causality assessment is "unknown but not related to investigational product," this should be clearly documented on study records.

In addition, if the investigator determines a serious adverse event is associated with study procedures, the investigator must record this causal relationship in the source documents and CRF, as appropriate, and report such an assessment in accordance with the serious adverse event reporting requirements, if applicable.

### **8.9. Exposure During Pregnancy**

This is a study exclusively in pregnant women. Enrolled subjects will be asymptomatic pregnant women who will receive study drugs for preventive treatment of malaria. All pregnancy-related AEs and pregnancy outcomes will be recorded on CRF pages as required clinical study data. Since all the information generally included on an Exposure In Utero (EIU) form will be collected on CRF paper, a separate EIU form is not required.

Subjects will be followed up to Day 28 post delivery (window: Day 28 to Day 42) for pregnancy outcomes or until pregnancy termination (ie, induced abortion). The reason(s) for an induced abortion should be specified.

If the outcome of the pregnancy meets the criteria for immediate classification as a serious adverse event (ie, spontaneous abortion, stillbirth, neonatal death, or congenital anomaly [including that in an aborted fetus, stillbirth or neonatal death]), the investigator should follow the procedures for reporting serious adverse events.

In the case of a live birth, the “normality” of the newborn can be assessed at the time of birth, or as soon thereafter as possible, and at Day 28 post delivery (window: Day 28 to Day 42). The “normality” of an aborted fetus can be assessed by gross visual inspection, unless pre-abortion test findings are suggestive of a congenital anomaly.

Additional information about pregnancy outcomes that are classified as serious adverse events follows:

- “Spontaneous abortion” includes miscarriage and missed abortion.
- All neonatal deaths that occur within 1 month of birth should be reported, without regard to causality, as serious adverse events. In addition, any infant death after 1 month that the investigator assesses as possibly related to the Exposure in Utero to the investigational medication should be reported.

Additional information regarding the Exposure in Utero may be requested by the investigator. Further follow-up of birth outcomes will be handled on a case-by-case basis (eg, follow-up on preterm infants to identify developmental delays). In the case of paternal exposure, the investigator must obtain permission from the subject’s partner in order to conduct any follow-up or collect any information.

### **8.10. Withdrawal Due to Adverse Events (See also Section on Subject Withdrawal)**

Withdrawal due to adverse event should be distinguished from withdrawal due to insufficient response, according to the definition of adverse event noted earlier, and recorded on the appropriate adverse event CRF page.

When a subject withdraws due to a serious adverse event, the serious adverse event must be reported in accordance with the reporting requirements defined below.

Unless a subject withdraws consent or leaves the town/village, she may be withdrawn from the study treatment but should continue in the study as we must follow them up for pregnancy outcome up to Day 28 post delivery.

### **8.11. Eliciting Adverse Event Information**

The investigator is to report all directly observed adverse events and all adverse events spontaneously reported by the study subject. In addition, each study subject will be questioned about adverse events.

### **8.12. Reporting Requirements**

Each adverse event is to be assessed to determine if it meets the criteria for serious adverse events. If a serious adverse event occurs, expedited reporting will follow local and international regulations, as appropriate.

#### **8.12.1. Serious Adverse Event Reporting Requirements**

If a serious adverse event occurs, Pfizer is to be notified within 24 hours of awareness of the event by the investigator. In particular, if the serious adverse event is fatal or life-threatening, notification to Pfizer must be made immediately, irrespective of the extent of available adverse event information. This timeframe also applies to additional new information (follow-up) on previously forwarded serious adverse event reports as well as to the initial and follow-up reporting of Exposure in Utero cases.

This timeframe of reporting within 24 hours also applies for the reporting of any medical device complaint.

In the rare event that the investigator does not become aware of the occurrence of a serious adverse event immediately (eg, if an outpatient study subject initially seeks treatment elsewhere), the investigator is to report the event within 24 hours after learning of it and document the time of his/her first awareness of the adverse event.

For all serious adverse events, the investigator is obligated to pursue and provide information to Pfizer in accordance with the timeframes for reporting specified above. In addition, an investigator may be requested by Pfizer to obtain specific additional follow-up information in an expedited fashion. This information may be more detailed than that captured on the adverse event case report form. In general, this will include a description of the adverse event in sufficient detail to allow for a complete medical assessment of the case and independent determination of possible causality. Information on other possible causes of the event, such as concomitant medications and illnesses must be provided. In the case of a subject death, a summary of available autopsy findings must be submitted as soon as possible to Pfizer or its designated representative.

**In addition, the Investigator will follow all applicable local and national safety reporting guidelines and regulations for notification to their local ethics and regulatory bodies.**

#### **8.12.2. Non-Serious Adverse Event Reporting Requirements**

All adverse events will be reported on the adverse event page(s) of the CRF. It should be noted that the form for collection of serious adverse event information is not the same as the adverse event CRF. Where the same data are collected, the forms must be completed in a consistent manner. For example, the same adverse event term should be used on both forms. Adverse events should be reported using concise medical terminology on the CRFs as well as on the form for collection of serious adverse event information.

#### **8.12.3. Medical Device Complaint Reporting Requirements**

Not applicable.

#### **8.12.4. Sponsor Reporting Requirements to Regulatory Authorities**

Adverse events reporting, including suspected serious unexpected adverse reactions, will be carried out in accordance with applicable local regulations.

### **9. DATA ANALYSIS/STATISTICAL METHODS**

Detailed methodology for summarization and statistical analyses of the data collected in this study will be documented in a Statistical Analysis Plan, which will be maintained by the sponsor. This document may modify the plans outlined in the protocol. However, any major modifications of the primary endpoint definition and/or its analysis will also be reflected in a protocol amendment.

#### **9.1. Sample Size and Power Determination**

Sample size will be determined using the observed primary endpoint pooled across both arms following a blinded review when approximately 1000 subjects achieve the primary endpoint.

The underlying true incidence of the primary endpoint in the control group is unknown, but has a substantial impact on the required sample size. To manage the uncertainty, the proportion of subjects experiencing a sub-optimal pregnancy outcome will be estimated from the current trial, when approximately 1000 subjects achieve the endpoint. This evaluation will be done in a blinded manner by the Sponsor study team, though the trial is open label. The underlying incidence will be estimated by the pooled (blinded) overall proportion of subjects experiencing a sub-optimal pregnancy outcome without regard to treatment group.

Total sample size will be determined using Table 4. For example, if the observed proportion of subjects experiencing a sub-optimal pregnancy outcome is found to be 0.30, then the total sample size will be 4206.

**Table 4. Sample Size Determination**

| Observed Pooled Proportion for The Primary Endpoint at N=1000 | $\leq 0.28$ | $>0.28$ to $\leq 0.32$ | $>0.32$ to $\leq 0.36$ | $>0.36$ to $\leq 0.40$ | $>0.40$ |
|---------------------------------------------------------------|-------------|------------------------|------------------------|------------------------|---------|
| Total Sample Size Required                                    | 5044        | 4206                   | 3552                   | 3030                   | 2602    |

Note that the total sample size required is calculated by employing a group sequential design as detailed in Section 9.5 with the upper bound of each interval assumed to be the true underlying proportion for the SP group.

Due to the adaptive nature of the sample size determination, operating characteristics of the study design in terms of power and Type I error rate were evaluated using simulations. Probabilities for early stopping for efficacy and futility at each of the interim analyses were evaluated as well. The design assumed a 20% risk reduction in the primary endpoint (relative risk=0.80, AZCQ/SP). A 23% risk reduction (relative risk=0.77, AZCQ/SP) was assumed for LBW (key secondary) given that early stopping for efficacy will only occur if both endpoints are positive. Type I error rates were simulated under the null hypothesis of no difference. Each scenario under the alternative hypothesis was run with 100,000 simulation iterations. One million iterations were used under the null hypothesis for each stated true proportion, for the primary endpoint.

#### 9.1.1. Simulated Power Under a 20% Risk Reduction

Simulated powers and futility probabilities assuming a 20% risk reduction (relative risk=0.80, AZCQ/SP) are presented in Table 5. The powers are approximately 90% for the true SP proportions  $\geq 28\%$ , which is the range for SP expected in this study. Power for LBW (relative risk=0.77) ranges between 82% and 88% approximately.

**Table 5. Power and Futility Probability: 20% Risk Reduction**

| True Proportion for the Primary Endpoint |       | Probability of Claiming Efficacy (%) |                    |           | Probability of Declaring Futility (%) |                    |                | Average Sample Size |
|------------------------------------------|-------|--------------------------------------|--------------------|-----------|---------------------------------------|--------------------|----------------|---------------------|
| SP                                       | AZCQ  | 1 st IA                   | 2 nd IA | Power     | 1 st IA                    | 2 nd IA | Beta (1-Power) |                     |
| 0.24                                     | 0.192 | 9                                    | 17                 | 81 | 1                                     | 3                  | 19             | 4492                |
| 0.28                                     | 0.224 | 15                                   | 23                 | 90 | <1                                    | 1                  | 10             | 4267                |
| 0.32                                     | 0.256 | 18                                   | 26                 | 92 | <1                                    | 1                  | 8              | 3677                |
| 0.36                                     | 0.288 | 20                                   | 26                 | 92 | <1                                    | 1                  | 8              | 3120                |
| 0.40                                     | 0.320 | 21                                   | 27                 | 93 | <1                                    | 1                  | 7              | 2679                |
| 0.44                                     | 0.352 | 22                                   | 27                 | 94 | <1                                    | 1                  | 6              | 2307                |

## Simulated Type I Error Rate Under the Null Hypothesis

Simulated Type I error rates for the primary endpoint are presented in Table 6. The Type I error rate is preserved at 0.0625% ( $\alpha=0.000625$  1-sided) within an allowable margin of error given the 1 million iterations performed.

**Table 6. Type I Error Rate**

| True Proportion for the Primary Endpoint |      | Probability of Claiming Efficacy (%) |                    |                   | Probability of Declaring Futility (%) |                    | Average Sample Size |
|------------------------------------------|------|--------------------------------------|--------------------|-------------------|---------------------------------------|--------------------|---------------------|
| SP                                       | AZCQ | 1 st IA                   | 2 nd IA | Type I Error Rate | 1 st IA                    | 2 nd IA |                     |
| 0.24                                     | 0.24 | 0.00340                              | 0.00470            | 0.06040    | 73                                    | 22                 | 2862                |
| 0.28                                     | 0.28 | 0.00430                              | 0.00600            | 0.05930    | 74                                    | 21                 | 2628                |
| 0.32                                     | 0.32 | 0.00310                              | 0.00740            | 0.06300    | 74                                    | 21                 | 2207                |
| 0.36                                     | 0.36 | 0.00320                              | 0.00530            | 0.05620    | 73                                    | 22                 | 1876                |
| 0.40                                     | 0.40 | 0.00260                              | 0.00580            | 0.06010    | 74                                    | 21                 | 1601                |
| 0.44                                     | 0.44 | 0.00350                              | 0.00820            | 0.05770    | 74                                    | 21                 | 1478                |

## 9.2. Efficacy Analysis

The primary efficacy analysis population (ie, Primary Analysis Set) will be intent-to-treat (ITT) for all endpoints. It will consist of subjects who are randomized, have received at least one dose of study medication (Day 0 at Visit 1 is considered the first dose of study medication), and have a single fetus. Subjects without the required data needed to compute an endpoint will be treated as missing. Analyses will also be performed for as per protocol analysis set, considered secondary. A per protocol analysis set will consist of all ITT subjects who have been compliant with study medication and will exclude subjects who have a neonate birth-weight measured greater than 7 days after birth if they do not already meet the definition of sub-optimal pregnancy outcome, and also exclude subjects who withdraw from study drug and switch to standard of care IPTp treatment. Compliance with study medication will consist of at least 6 of the 9 AZCQ daily doses, and at least 2 of the 3 SP daily doses. Once again, subjects without the required data needed to compute an endpoint will be treated as missing. Sensitivity analyses will be defined for both the ITT and PP populations.

Treatment group comparisons for the primary endpoint will use an overall alpha level of 0.00125 2-sided (equivalent to 0.000625 1-sided), subject to the alpha spending function specified in Section 9.5. Treatment group comparisons for the secondary endpoints will use an overall alpha level of 0.05 2-sided (equivalent to 0.025 1-sided), also subject to the same alpha spending function.

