#### **4.3. Randomization Criteria**

A computer-generated randomization list will be provided by the sponsor to the investigators. Randomization will be stratified according to gravidae (primigravidae & secundigravidae vs. other gravidae). Among all gravida, approximately 50% subjects will be stratified with primigravidae & secundigravidae. The investigator will assign subject identification numbers sequentially as they are determined to be eligible for treatment (PID numbers). This unique PID number will be retained throughout the study and must appear on all case report form (CRF) pages, source documents and lab data. The eligible subjects who have met all inclusion/exclusion criteria will receive study medication assigned to the next available randomization number at the Day 0 during the first study visit. The randomization number will also be recorded on the proper CRF page.

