## 5. STUDY TREATMENTS

The Study treatment is a fixed dose tablet formulation of AZ and CQ (AZCQ) containing 250 mg AZ and 155 mg CQ base. Comparator drug is SP and will be supplied as Fansidar® (Roche) tablet (500 mg sulfadoxine/25 mg pyrimethamine). Subjects will be randomized in 1:1 ratio to receive either AZCQ or SP IPTp regimens. Both regimens will consist of three treatment courses. The treatment courses of AZCQ and SP will consist of the following:

1. **AZCQ treatment course:** 1000 mg AZ and 620 mg of CQ base (4 combination tablets of AZCQ with individual strength of 250 mg/155 mg), by mouth (PO) once daily for 3 days (Days 0, 1, 2);

OR

2. **SP treatment course:** 1500 mg sulfadoxine and 75 mg pyrimethamine (3 fixed tablets of SP strength at 500 mg/25 mg), PO single dose once daily on Day 0.

Each subject will receive three IPTp treatment courses of AZCQ or SP during ANC visits at 4 - 8 week intervals. The first treatment course will be administered during the second trimester (14-26 weeks of gestation as confirmed by ultrasound). The last treatment course should be given to subjects prior to or during 36 weeks of gestation.

The first dose of each AZCQ treatment course will be administered under supervision during the ANC visits. Subsequent two doses of AZCQ will be administered at home under supervision by the fieldworker(s).

Each dose of SP treatment will be administered under supervision during the ANC visits.

Please note that the terms course and dose are often used synonymously in IPTp studies using SP because only one directly observed dose is required per treatment course. Within this protocol, dose represents medications taken on a given day; course means all medications required for a complete treatment at one visit.

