## 5.2. Breaking the Blind

The study is open label. However, the microbiologists (microscopists) will be blinded to the study treatments of the subject and the reading of other microscopists. The lab scientists undertaking the laboratory investigations (ie, molecular assays, biochemical assays, histological and microbiological investigations) will be unaware of the study group from which the sample was obtained.

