### 5.3.3. Administration

All study drugs will be administered as open label therapy under supervision. Study medication will be dispensed by the Investigator or designee (Section 5.3.2). AZCQ and SP should not be administered on an empty stomach. Each dose should be administered with a glass of water.

- AZCQ treatment: first dose of each AZCQ treatment course will be administered under supervision during the ANC visit. Subsequent two doses will be administered at home by fieldworker(s).

- SP treatment: each dose of SP treatment course will be administered under supervision during the ANC visit.

Each subject will receive three IPTp treatment courses of AZCQ or SP during ANC visits at 4 - 8 week intervals. The first treatment course will be administered during the second trimester (14-26 weeks of gestation as confirmed by ultrasound). The last treatment course should be given to subjects prior to or during 36 weeks of gestation.

Any dose that is vomited within 30 minutes of administration will be repeated. If vomiting re-occurs after the re-dose, the subject will not receive further study treatments but will be referred to the investigator and will be given standard ANC care. If subjects in AZCQ group vomit after re-dose during first or second treatment course, they will be given additional course(s) of standard IPTp courses with SP. If vomiting on re-dosing of AZCQ happens during the home visits, subject will be advised to return to the study site within 7 days for appropriate treatment by the study physician. All subjects will be followed through Visit 6 on Day 28 (window Day 28 - Day 42) post delivery.

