**Refer to Section 7 (Assessments) for details on the procedures performed in the study.**

### **6.1. Study Period**

#### **6.1.1. Visit 1: Baseline/Screening Visit/Treatment Course 1**

##### Day 0: Antenatal Care (ANC) Visit/Assessment of Study Eligibility

After informed consent is obtained, the subject must have the following procedures performed prior to the start of therapy:

- Medical history;
- Obstetrical history;
- Concomitant treatment history;
- Urine pregnancy test (if not done at any prior ANC visit for this pregnancy);
- Urine analysis for glucose and proteins;
- Complete physical examination;

- Vital signs;
- Routine obstetric checkup;
- Obstetrical ultrasound examination (if urine pregnancy test is positive);
- Hemoglobin level (with HemoCue™);
- *T. pallidum* screen test if not done at previous ANC check up;
- Nasopharyngeal swab test for macrolide resistant and penicillin resistant *Streptococcus pneumoniae* in approximately 600 subjects each in AZCQ and SP arms from 2 or more sites as feasible.

#### Day 0: Post Assessment of Eligibility/Treatment Course 1

Subjects who have met all inclusion/exclusion requirements and are eligible to be randomized will have the following procedures performed:

- Randomize to one of the study treatments;
- Administer treatment (AZCQ or SP);
- Assess adverse (AE) events;
- Provide LLINs.

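### The primary set called intent-to-treat leaves out randomized women who took no dose, in an open-label trial where the arm can be known before dosing

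*Protocol*

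**What the plan says.** Section 9.2 states: "The primary efficacy analysis population (ie, Primary Analysis Set) will be intent-to-treat (ITT) for all endpoints". The next sentence narrows the set: "It will consist of subjects who are randomized, have received at least one dose of study medication", and a single fetus is also required. Section 9.2.1 rests the primary test on this set. Section 9.2 promises sensitivity analyses, but only for the intent-to-treat and per protocol populations; no analysis of all randomized women is named.

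Section 5.2 says "The study is open label", with blinding only for microscopists and laboratory scientists, and Section 5.3.3 says "All study drugs will be administered as open label therapy under supervision". In Section 6.1.1, after eligibility is confirmed on Day 0, the first step is "Randomize to one of the study treatments" and the second is giving the drug. Under Section 4.3 an eligible woman "will receive study medication assigned to the next available randomization number at the Day 0 during the first study visit".

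Section 9.2.1 counts loss to follow-up before the pregnancy ends, and a missing birth weight, as sub-optimal outcomes.

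**The concern.** Leaving out undosed women is harmless when the reason for not dosing cannot depend on the arm. Here a woman, or the staff, can know the allocation before the first dose. Section 5.1 guards the decision to enrol and the order of enrolment against knowledge of treatment; it does not cover what happens between allocation and dosing.

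The exclusion also sits badly with the endpoint. A woman who takes one dose and then disappears is a failure in her arm. A woman who declines on learning her arm and then disappears is in neither numerator nor denominator. If such women come mainly from one arm and are at higher than average risk, that arm looks better than it is. The primary superiority claim, tested at a very strict alpha, rests on this set.

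**Working it through.** **Inputs.** One-sided alpha 0.000625, power about 90%, looks at 50%, 70% and 100%, gamma(-4) alpha spending, gamma(-6) beta spending and non-binding futility (Section 9.5). Risk ratio 0.80, with the SP risk at the upper bound of each Table 4 interval (Section 9.1). Allocation 1:1 (Section 5). The last Table 4 interval is open; 0.44 is assumed for it, the highest SP risk in Table 5. The protocol gives no rate of randomized but undosed women, so the rates below are assumptions.

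**Step 1: reproduce Table 4.** With q = 0.8p, the fixed-sample size on the log risk ratio scale is

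N = 2 × (z_alpha + z_beta)² × [(1−p)/p + (1−q)/q] / ln(0.8)².

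At p = 0.28: (3.227 + 1.282)² = 20.33; the bracket is 2.571 + 3.464 = 6.036; ln(0.8)² = 0.0498. N is about 4,928. The group-sequential design inflates this by 1.0235, giving 5,044. The five intervals give 5,044, 4,205, 3,552, 3,030 and 2,602, against 5,044, 4,206, 3,552, 3,030 and 2,602 in Table 4. The formula reproduces the table with no allowance for undosed women.

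**Step 2: selection when there is no true effect.** Let both arms have risk p. A fraction d of the AZCQ arm is undosed and dropped, with risk r; none are dropped from SP. The remaining AZCQ risk is q* = (p − d·r)/(1 − d), and the apparent risk ratio is q*/p. The error is for a single-look Wald test on the log risk ratio at one-sided 0.000625.

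Worked case, p = 0.28, N = 5,044 (2,522 per arm), d = 0.01 (25 women), r = 0.56:
- q* = (0.28 − 0.0056)/0.99 = 0.2772, so the risk ratio is 0.990.
- SE = √[0.7228/(0.2772 × 2,497) + 0.72/(0.28 × 2,522)] = 0.0454.
- Shift = 0.01015/0.0454 = 0.223, and the error is Φ(−3.227 + 0.223) = 0.0013, about 2.1 times nominal.

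With d = 0.02 (50 women) the risk ratio is 0.980 and the error 0.0028, about 4.4 times nominal.

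| Risk of dropped women | p = 0.28, N = 5,044: 1% dropped | 2% dropped | p = 0.44, N = 2,602: 1% dropped | 2% dropped |
|---|---|---|---|---|
| Average | 0.000625 | 0.000625 | 0.000625 | 0.000625 |
| 1.5 times average | 0.00092 | 0.0013 | 0.00093 | 0.0014 |
| Twice average | 0.0013 | 0.0028 | 0.0014 | 0.0028 |
| All would be events | 0.0040 | 0.0196 | 0.0017 | 0.0041 |

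**Step 3: a true benefit, for contrast.** With SP risk 0.32 and a risk ratio of 0.80 in dosed women, the all-randomized AZCQ risk is 0.256(1 − d) + r·d. At d = 1% the risk ratio is 0.802 if undosed women have the SP risk and 0.823 if all are events. At d = 3% it is 0.806 and 0.870. The lower figure in each pair is dilution from including untreated women, not evidence of bias in the dosed set.

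**The case against.** The strongest reply is that the window is very short. Randomization and the supervised first dose fall at the same Day 0 visit (Sections 4.3 and 6.1.1). Inclusion criteria 3 and 4 require willingness to follow the treatment plan and agreement to supervised dosing; exclusion criteria 8 and 12 remove women who cannot take tablets or will not follow the protocol. All this precedes allocation. It stands, and it makes a large number of undosed women unlikely.

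A reader might infer that the heavier AZCQ regimen, 12 tablets over three days with home visits against three tablets once, drives unequal exclusion. The documents support little of that. One dose secures membership, and the first dose is four tablets against three (Section 5). A woman who stops after it stays in the set. Only foreknowledge of the later doses could act beforehand.

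A reader might also infer that the exclusion must favour the arm refused more often, or that a false superiority claim has been shown. Neither follows. Inflation in AZCQ's favour needs exclusion concentrated in AZCQ and above-average risk in those excluded; lower-risk exclusions from AZCQ would work against it.

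Nor does the label conceal anything: the dosing condition is in the sentence directly after it. And the statement that "A computer-generated randomization list will be provided by the sponsor to the investigators" bears on allocation concealment, a separate question.

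What the reply does not remove is the design fault: entry to the primary set is decided after an open allocation, with no all-randomized analysis beside it.

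**Conclusion.** The point holds in limited form. The primary set is a randomized-and-dosed set under an intent-to-treat name. In this open-label design, membership can depend on knowledge of the arm, and undosed women who leave are handled in the opposite way to dosed women who leave.

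The likely number is small and unknown. With no true effect and average risk in the excluded women, the error stays at 0.000625. Because that alpha is so strict, 1% to 2% arm-specific exclusion of women at twice average risk is enough to raise the error to about 0.0013 to 0.0028. Those figures rest on assumed rates, no exclusions on SP and a single-look test. They show sensitivity, not an expected bias. The change is worth making because it removes the question at little cost.

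**What to change.** In Section 9.2, define the primary set as all randomized women with a singleton pregnancy, analysed by assigned arm regardless of dosing. Follow undosed women to delivery, as Sections 6.2 and 8.10 already do for women off study treatment, and apply the failure rule in Section 9.2.1 as it stands. Report the number of randomized but undosed women by arm. Keep the dosed-only set, renamed modified intent-to-treat, as a sensitivity analysis. Section 9 says major changes to the primary analysis will also be reflected in a protocol amendment, so this belongs in the protocol.

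The cost is wording, follow-up of a few extra women and a possibly slightly less favourable estimate. Table 4 need not change. At SP risk 0.28 and N = 5,044, single-look power is 91.2%. If 1% of AZCQ women (none on SP) are undosed and carry the SP risk, the all-randomized risk ratio is 0.802 and power 90.5%. If every one of them were lost and so counted as a failure, these become 0.828 and 75.8%, which is a reason to follow them.
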